## Introduction

### Background and Rationale

Movement is essential for musicians, enabling them to express creativity and connect with their audience. The integration of body and instrument creates an impression of effortless harmony, free from tension and pain. However, this idealized image often obscures the reality of musculoskeletal and neurological disorders that can affect musicians, limit performance, and, in some cases, end careers prematurely. Musicians often ignore pain and symptoms that need attention and rest [1].

Bernardino Ramazzini first described occupational diseases in musicians in 1713. Zaza et al [2] introduced the term playing-related musculoskeletal disorders (PRMDs) to describe musculoskeletal symptoms, such as pain, weakness, numbness, or loss of coordination, that are caused or exacerbated by playing a musical instrument and are severe enough to impair a musician’s ability to perform at their usual technical level. In this definition, a condition qualifies as a PRMD only when it interferes with musical performance, distinguishing it from symptoms that may occur in everyday life but do not affect playing. Zaza et al [2] further emphasized that PRMDs can become chronic and disabling, affecting musicians not only physically but also emotionally and socially [3]. Reviews report high prevalence rates of musculoskeletal disorders among musicians, with rates ranging from 57% to 68% for general issues, 9% to 68% for PRMDs, and 62% to 93% for one-time PRMDs [1,4,5]. Studies, such as those by Fishbein et al [6], show that many musicians, including 76% of International Conference of Symphony and Opera Musicians members, experience medical issues that compromise their performance.

Identifying risk factors for PRMDs is crucial for prevention [7]. Common factors include gender, age, professional status, years of experience, type of instrument, repertoire, technique, long practice hours, poor physical condition, muscle fatigue, lack of preventive behaviors, and previous injuries. Psychological stress factors, such as anxiety, depression, and perfectionism, also correlate with musculoskeletal disorders [1,4,8]. The weight of the instrument and playing posture can influence injury prevalence.

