Participants were seated on a standardized stool (height: 47 cm; leg separation: 26.5 cm), except for the double bass players who used a chair provided by the orchestra without a backrest due to the instrument’s size and ergonomic requirements. The stool, the chair, and the camera were placed in fixed positions, which were marked on a mat included in the kit, and the instrument was calibrated according to these distances.

For photos without the instrument, participants kept their arms relaxed alongside the body. For photos with the instrument, hand placement followed the standard playing position (a position for string instruments). In both phases, the Physical Analyzer Portable will be used—a noninvasive, portable device that allows calibrated photo acquisition on the frontal and sagittal planes and subsequent data processing through dedicated software. This device is not formally validated but it is aligned with the principles of clinical posture assessment presented in the study by Fortin et al [19]. The following measurements will be taken with and without the musical instrument.

As far as the frontal plane is concerned, the following parameters will be measured: trunk inclination on the frontal plane: angle between C7 and IG, head-neck inclination: angle between ST and GL, right shoulder height: distance between RS and the horizontal line passing through C7, left shoulder height: distance between LS and the horizontal line passing through C7, right shoulder width: distance between RS and the vertical line passing through C7, left shoulder width: distance between LS and the vertical line passing through C7, right scapula–rachis distance: distance between RIA and the vertical line passing through C7, and left scapula–rachis distance: distance between LIA and the vertical line passing through C7.

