As far as the sagittal plane is concerned, the following parameters will be measured: cervical arrow: distance between the vertical tangent to the apex of the dorsal kyphosis and C7, lumbar arrow: distance between the vertical tangent to the apex of the dorsal kyphosis and L3, right shoulder distance: distance between RS and the vertical line passing through C7, and left shoulder distance: distance between LS and the vertical line passing through C7. We will numerically quantify trunk rotation and right-left shoulder asymmetry in both conditions (with and without the instrument). Furthermore, we will compute all between-condition differences to assess postural changes attributable to instrument use. All distances are measured in millimeters, and all angles are measured in degrees.

Musical instruments will be classified into 2 main categories: symmetric and asymmetric [11], and the postural measures will be analyzed based on this categorization. Further exploratory analyses may also be conducted on specific instrument families.

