### Association With Pain and Disability (Secondary Aims)

To examine factors associated with the outcomes of pain and performance-limiting pain, logistic regression models will be used. The dependent variables will be the presence of pain during the preceding week and the presence of performance-limiting pain during the preceding week, both operationalized as binary outcomes. Independent variables will include demographic characteristics (eg, age and gender), occupational factors (eg, instrument type [classified as symmetric or asymmetric], years of professional experience, and practice hours), and postural delta values, which represent instrument-induced postural changes as described above.

To investigate factors associated with the severity of disability, as measured by the QuickDASH, Oswestry Disability Index, and Neck Disability Index scores, linear regression models (or quantile regression models, if model assumptions are violated) will be used, incorporating the same set of independent variables.

Variables achieving a *P* value of <.10 in univariate analyses will be entered into multivariable models to identify independent predictors. Results will be reported as odds ratios or regression coefficients with their corresponding 95% CIs. A *P* value of <.05 will be considered indicative of statistical significance in all final models.

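### A univariate P<.10 screen decides which of at least 19 candidates enter the pain and disability models, so known risk factors can drop out and selected effects are overstated

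*Protocol article*

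**What the plan says.** The rule is in the protocol article under Association With Pain and Disability (Secondary Aims).

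- **Candidates.** "Independent variables will include demographic characteristics (eg, age and gender", then occupational factors: instrument type, "years of professional experience, and practice hours), and postural delta values, which represent instrument-induced postural changes". Both covariate lists are given as examples, so they are not closed.
- **Entry.** Variables with P<.10 "in univariate analyses will be entered into multivariable models to identify independent predictors". No variable is exempt from the screen.
- **Reporting.** "Results will be reported as odds ratios or regression coefficients with their corresponding 95% CIs". The significance threshold in every final model is .05.
- **Outcomes.** Two binary outcomes for the preceding week (pain, and performance-limiting pain) and three disability scores, all with the same independent variables.

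The deltas come from the measures in Interventions and Outcomes. These include "left shoulder height: distance between LS and the horizontal line passing through C7", its right-sided counterpart, and two further quantities: "We will numerically quantify trunk rotation and right-left shoulder asymmetry in both conditions". No formula is given for asymmetry.

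Handling of Multiple Postural Measures names three core parameters (head-neck inclination, shoulder asymmetry, lumbar arrow). It applies Bonferroni or Benjamini-Hochberg correction to the paired comparisons. Neither the core set nor the correction is carried into the regression section.

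**The concern.** Background and Rationale lists gender, age, years of experience, type of instrument and long practice hours among the common risk factors for playing-related disorders. The article also argues that the instrument shapes posture. On its own account, then, these variables can confound the relation between a postural delta and pain. Yet any of them leaves the model if its univariate P value in this sample is .10 or more. A univariate P value does not show whether a variable confounds, least of all when confounding masks the variable's own crude association.

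The second problem is that selection and estimation use the same data. A delta enters only if its observed association is large enough, so entering estimates are on average too far from zero. The ordinary CI treats the model as if it had been fixed beforehand.

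This matters because the Objective in the Abstract places association with pain in the primary aim, and the Discussion expects the results to inform ergonomic interventions.

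**Working it through.** **1. The only sample-size figure.** Sample Size gives a 6% half-width at 50% prevalence. 1.96 × √(0.25/250) = 0.062, which rounds to 6%. It concerns prevalence; no figure is given for the regressions.

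**2. Number of candidates.** 8 frontal + 4 sagittal measures + trunk rotation + shoulder asymmetry = 14 deltas. Adding age, gender, instrument type, years of experience and practice hours gives 14 + 5 = 19. This is a minimum: Ethical Considerations also mentions physical activity and scoliosis. If all 19 were null and independent, 19 × 0.10 = 1.9 would be expected to pass, and at least one would pass with probability 1 − 0.90^19 = 0.86.

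**3. Simulation.** n = 250, 19 standard normal candidates, logistic outcome, univariate Wald P<.10, then a joint model; 600 runs per scenario (Monte Carlo standard error at most √(0.25/600) = 2 percentage points). The documents give no prevalence, effect size or correlation for this cohort, so those below are assumptions.

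| Scenario | Prevalence 20% | Prevalence 50% |
|---|---|---|
| Confounder (OR 1.25, correlation 0.5 with a null exposure) screened out | 60% | 45% |
| Mean reported OR of that null exposure when it passes | e^0.199 = 1.22 | e^0.142 = 1.15 |
| Confounder acting against the exposure (OR 1/1.25, exposure OR 1.5) screened out | 90% | 90% |
| True OR 1.30, mean reported OR when it passes | e^0.395 = 1.48 | e^0.348 = 1.42 |
| CI coverage for that true OR when it passes | 0.96 | 0.97 |

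Mean ORs are averaged on the log scale. A repeat of the simulation gave 46% to 61% for the dropped confounder and 1.41 to 1.48 for the OR of 1.30. At 50% prevalence an unscreened 19-term model already averages 1.33 for a true 1.30, so a small part of the excess is ordinary small-sample bias.

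**4. What the screen does not cause.** Chance of at least one null term with P<.05, with the screen versus with all 19 terms entered:

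- independent candidates: 64% versus 69% (prevalence 20%), 60% versus 65% (50%);
- pairwise correlation 0.3: 29% versus 65% (20%), 24% versus 62% (50%).

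For comparison, 1 − 0.95^19 = 62%. The screen leaves this rate about the same or lowers it.

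**5. Collinearity.** With an intercept, the right and left shoulder-height deltas and their signed difference, the design matrix has rank 3 of 4, so the dependency is exact. If asymmetry is an absolute difference, the rank is 4 of 4.

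**6. Events per term (binary outcomes; smaller outcome group ÷ terms).** The Background's review range, "9% to 68% for PRMDs", is not a one-week prevalence in this cohort and serves only as an outer range.

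| Assumed prevalence | Smaller group | 19 terms | 8 terms |
|---|---|---|---|
| 9% | 22.5 | 1.2 | 2.8 |
| 20% | 50 | 2.6 | 6.3 |
| 50% | 125 | 6.6 | 15.6 |
| 68% | 80 | 4.2 | 10.0 |

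**The case against.** The strongest defence is that the plan hedges. It calls all postural measures exploratory, promises effect sizes and judicious interpretation, heads these models as secondary, and acknowledges that the design cannot establish causation. The covariate lists are examples, so an analysis plan may hold a fuller set. Part of this stands: the consequences are those of an exploratory analysis. But the entry rule is stated outright, and a longer candidate list under the same rule would still be screened. The Abstract also puts the pain association in the primary aim.

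Three stronger readings are tempting, and the documents do not support them.

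- **That the screen creates a 60% risk of a false predictor.** Step 4 shows that the risk is as high or higher without it. It comes from 19 tests at .05.
- **That about half of the null variables entering have a CI excluding 1, against a nominal 5%.** This is nearly arithmetic: among null P values below .10, about half lie below .05. Comparing that conditional rate with an unconditional 5% misleads.
- **That several candidates are exactly collinear.** At most one dependency can be shown. It requires a signed right-minus-left height difference, which the article does not define, and all three terms passing the screen. Main Comparison's mention of a shoulder height difference suggests that reading but does not settle it.

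Few events per term is also not a given. It depends on an unknown prevalence and does not apply to the linear or quantile models for the disability scores.

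**Conclusion.** The concern holds in a limited form. The screening rule is a poor choice that the article fixes explicitly, and it does two kinds of damage: it can remove risk factors that the article itself names, and it pushes selected estimates away from zero. Under the assumptions shown, a moderate confounder is dropped in about 45% to 60% of runs, and a true OR of 1.30 is reported as about 1.41 to 1.48 at prevalences of 50% to 20%. These sizes would change with other prevalences, effects and correlations.

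The CIs fail in the sense that they ignore selection. For the true effect simulated, coverage stayed near 0.96, so the visible fault there is bias rather than narrow intervals. Multiplicity across the regression deltas is a separate gap that removing the screen does not close. The matter should be changed, but it does not threaten the paired with/without-instrument comparison.

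**What to change.** 1. Delete the P<.10 screen.
2. Force the same eight terms into every model: age, gender, instrument category, years of experience and practice hours, plus the deltas for head-neck inclination, shoulder asymmetry and lumbar arrow. Age and years of experience will probably correlate, so their own coefficients should not be over-read.
3. Fit each remaining delta singly with the five covariates and label those results exploratory.
4. Extend the Bonferroni or Benjamini-Hochberg correction already planned for the paired tests to the regression deltas, and choose one. Unadjusted, three independent core deltas carry 1 − 0.95^3 = 14.3% per model; the full 14 carry 1 − 0.95^14 = 51%.
5. Define shoulder asymmetry (signed or absolute) and never enter it together with both shoulder heights.
6. Use Firth logistic regression if performance-limiting pain has few events per term, with the threshold set in advance (for example, about 10).

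The cost is mainly wording. Some forced terms will be non-significant, CIs may be slightly wider, and Firth regression may need an SPSS extension or R. Results states that full analysis is under way, so the change should be made and dated now, and reported as made after analysis began.

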### Statistical Methods

Statistical analysis will be performed using SPSS Statistics software (version 27.0; IBM Corp). The primary analysis will focus on within-subject comparisons of postural parameters measured in the 2 experimental conditions (without instrument vs with instrument). Continuous variables will be described using the mean and SD or the median and IQR based on their distribution. The Kolmogorov-Smirnov test will be used to assess the normality of the distributions. Categorical variables will be reported in terms of relative frequencies.

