### Handling of Multiple Postural Measures

Given the multiplicity of postural parameters assessed, there exists an inherent risk of type I error inflation due to multiple comparisons. To mitigate this, several strategies will be implemented. Although all postural measures are considered exploratory, the analysis will prioritize a core set of clinically relevant parameters identified a priori based on the extant literature, including head-neck inclination, shoulder asymmetry, and lumbar arrow. As an alternative to multiple univariate comparisons, multivariate analysis of variance for repeated measures may be used to compare the overall postural profile between conditions, provided the underlying assumptions are satisfied. For exploratory analyses involving multiple univariate paired comparisons, conservative corrections such as the Bonferroni adjustment or false discovery rate control using the Benjamini-Hochberg procedure will be applied. Findings will be interpreted judiciously, and effect sizes, including Cohen *d* for paired samples, will be reported alongside *P* values to emphasize the magnitude of observed effects rather than relying solely on statistical significance.

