## Results

The study protocol was approved by the ethics committee in November 2022. Data collection initially was scheduled to take place over a 20-month period from May 2023 to December 2024. However, to ensure the achievement of a robust and representative sample size, the recruitment period was extended through April 2026. As of February 2026, a total of 240 participants had been successfully recruited across all participating clinical sites, approaching the predefined target sample size of 250. Preliminary data cleaning and descriptive analyses were initiated in February 2026, with full statistical analysis currently underway. On the basis of the current progress of the study, final results are expected to be available for publication by July 2026.

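### The plan corrects the paired posture tests for multiplicity but reads the same postural deltas at an unadjusted .05 in models for five pain and disability outcomes

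*Protocol article*

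**What the plan says.** Three parts of the protocol article bear on this.

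- **Handling of Multiple Postural Measures** names the risk of type I inflation from the number of parameters. Its correction is tied to one set of tests: "For exploratory analyses involving multiple univariate paired comparisons, conservative corrections". Bonferroni and Benjamini-Hochberg are given as the candidate methods. The optional multivariate analysis of variance in that section also compares only the two conditions.
- **Main Comparison** defines each delta (with instrument minus without) and says the deltas become key independent variables in the later regressions.
- **Association With Pain and Disability (Secondary Aims)** uses logistic models for pain and for performance-limiting pain in the preceding week, and linear or quantile models for QuickDASH, Oswestry and Neck Disability Index scores. Variables with a P "value of <.10 in univariate analyses will be entered into multivariable models to identify independent predictors". A P "value of <.05 will be considered indicative of statistical significance in all final models". No adjustment is mentioned.

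The heading of that last section ranks the association as secondary. The Objective in the Abstract includes it in the primary aim.

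**The concern.** The reason given for correcting the paired tests, namely many postural parameters, applies with more force to the regressions, where the same parameters are tested against five outcomes. The plan protects the question of whether posture changes when the instrument is held. It leaves unprotected the question of whether that change goes with pain or disability. The second question is the one from which the article hopes to identify associated factors and inform ergonomic measures. A few chance findings, reported as significant independent predictors, could be taken for instrument-specific associated factors.

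**Working it through.** **The plan's own figure.** The article gives no error rate for the models. Its one design figure is a 6% half-width for a 50% prevalence with 250 participants: 1.96 x sqrt(0.5 x 0.5 / 250) = 0.062, which is 6% to the whole percent. It has no bearing on this point.

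**Inputs from the article.**

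- Postural parameters: 8 in the frontal plane and 4 in the sagittal plane, so 12. Adding trunk rotation and right-left shoulder asymmetry gives 14. This is a count from the Interventions and Outcomes section. Shoulder asymmetry may overlap with the separate right and left shoulder measures, hence 12 to 14.
- Outcomes in the models: 2 binary + 3 scores = 5.
- Screen: P<.10. Final threshold: P<.05. Sample size: 250.

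**Step 1: independent tests, no true association.** Expected false positives = 0.05 x m. Chance of at least one = 1 - 0.95^m.

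| Family | m | Expected false positives | Chance of at least one |
|---|---|---|---|
| 14 deltas, one outcome | 14 | 0.70 | 51% |
| 3 named core parameters x 5 outcomes | 15 | 0.75 | 54% |
| 12 deltas x 5 outcomes | 60 | 3.0 | 95% |
| 14 deltas x 5 outcomes | 70 | 3.5 | 97% |

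**Step 2: the stated rule with correlated measures.** Independence is a worst case, because several distances share C7 as reference. The procedure was therefore simulated with no true associations: n=250, 14 deltas, five outcomes, screen at P<.10, then a joint model read at P<.05. The article gives no correlations, so they are assumed. Linear models with Gaussian outcomes stand in for the mix of logistic and linear models. Outcome correlations of 0 and 0.5 were tried, with 3000 runs per setting.

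| Assumed correlation between deltas | Chance of at least one false posture finding, five outcomes |
|---|---|
| 0 | about 94-97% |
| 0.3 | about 74-78% |
| 0.5 | about 47-50% |
| 0.7 | about 23-27% |

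For a single outcome the corresponding chances are about 50%, 27% and 13% at correlations of 0, 0.3 and 0.5.

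**Step 3: does a simple correction work?** The screen matters here.

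- Benjamini-Hochberg at 5%, applied only to coefficients that survived the P<.10 screen, still gave at least one false finding in about 46-49% of runs at correlation 0, 30-31% at 0.3 and 12% at 0.5. The surviving coefficients have already been selected for small P values.
- With the family counted as all 70 candidate tests, the rate was about 6% or less.
- With all 14 deltas kept in every model and Benjamini-Hochberg applied to their coefficients, the rate was about 5%.

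For scale, a lone finding in a family of 70 would need P ≤ 0.05/70 = 0.00071.

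**The case against.** The best defence is that these are exploratory analyses. The article says so ("Although all postural measures are considered exploratory"), heads the models as secondary aims, promises cautious interpretation, effect sizes and 95% CIs, and acknowledges reverse causality. Many statisticians would not require family-wise control of secondary observational regressions. This lowers the weight of the point but does not answer it. The plan chose to correct paired tests that it also calls exploratory, and it applies the language of significance and independent prediction to the models. Cautious interpretation sets no error rate. Nor is the .05 rule a detail left open for a later document: it is stated, for all final models.

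The defence is also right that 97% is an upper bound. The range in the working is the fairer figure.

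A reader might infer more than the article supports:

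- **Choices made with the data in view.** The core set is given by example, the correction method and the multivariate option are left open, and the article reports analysis "with full statistical analysis currently underway". But it also says the core set was identified a priori, and it dates the descriptive work, not these choices. A condensed article may leave the full list and method to the full plan. Nothing shows data-driven selection.
- **A contradiction between primary and exploratory.** Statistical Methods says "The primary analysis will focus on within-subject comparisons", while the measures are called exploratory. The first ranks the analyses and the second describes the evidential status of the measures. Both can hold.

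**Conclusion.** The mismatch stands on the text. Multiplicity is acknowledged for the postural parameters and corrected for the paired tests. It is then ignored where the same parameters are tested against five outcomes, in an association that the Abstract counts as part of the primary aim. With no true associations, the chance of at least one false posture finding runs from about 23% (delta correlation 0.7) to about 97% (independence), against a nominal 5%. The size rests on the count of 12 to 14 deltas, the assumed correlations and the linear stand-in. The direction does not: every setting tried was well above 5%. The design is not invalidated, but the rule should be changed before the posture-pain results are reported.

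**What to change.** In the section on association with pain and disability, choose one of two routes.

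1. **Control the error rate.** Apply Benjamini-Hochberg, which the plan already names, at 5% to the posture coefficients across the five outcomes. Define the family as all candidate delta-outcome tests (for example 14 x 5 = 70), not only those that pass the P<.10 screen. Alternatively, drop the screen for the deltas, keep all of them in each model and apply the same procedure to their coefficients. Dropping the screen without a correction would not help, since 70 x 0.05 = 3.5 false positives would still be expected with no true associations.
2. **Report as exploratory.** Give the posture coefficients as estimates with 95% CIs, and remove the .05 significance rule and the predictor wording for them.

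Either route takes a few sentences and, for the first, a few lines of code. No new data are needed. The price is that fewer posture-pain associations will be called significant. Keeping all deltas in each model also means larger models, which may be demanding if either pain outcome turns out to be uncommon.
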